### Liver biopsies

The ultrasound-guided liver biopsy will be performed at baseline and endpoint visits as previously described (2013_207). If a liver biopsy is already performed 12 months prior to screening, no need for baseline biopsy. After an overnight fast, the subject will be in supine position, and using an ultrasound a non-vascularised segment of the right liver lobe will be identified. A needle of 14 to 19 gauge will be used for the biopsy, and the patient will be asked to hold their breath during the biopsy. Afterwards a bandage will be put on the puncture site. The total estimated time for the biopsy is 15-30 minutes. The subject is then instructed to lie on his/her right side for 1-2 hours after the test, and pulse, blood pressure and temperature are checked after the biopsy. All samples will be stored both in formalin/paraffin and frozen in liquid nitrogen after extraction, and stored at -80°C until analysis. Ultrasound-guided percutaneous liver biopsy is a safe method at our hospital with a low complication rate (typically self-limiting bleeding) of less than 0.1% (Sporea, Popescu, & Sirli, 2008).

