**Nature and extent of the burden and risks associated with participation, benefit and group relatedness:**

This study is a continuation of our previous intervention studies aiming to study underlying mechanisms of gut microbiota in liver gene expression in NALFD-NASH subjects (MASH study 2013_207) and our study on the role of microbiota on muscle gene expression and glucose metabolism (APPETITE study 2014_084). Oral microbiota is studied by taking an oral swab of the upper front teeth rime in overnight fasted subjects that refrained from tooth brushing that morning (FATMED study 2016_117). Moreover, we currently are building a large prospective cohort of patients with NAFLD-NASH to follow the natural course of (liver biopsy proven) changes in NAFLD-NASH between baseline and after 5 years (2017_311). Participants will be recruited from our outpatient clinics. An ultrasound or transient electrography will be performed to establish hepatic steatosis, if they do not already have an existing diagnosis. All subjects will in total have six site study visits, and total 21 hours in 12 weeks. At each visit we will collect blood and fecal samples. In addition, body weight will be measured at each visit. Other anthropometrics including height and waist circumference will be screened at baseline. At the baseline (first) and endpoint (final) visit we will collect (ultrasound guided) liver, muscle and subcutaneous adipose tissue biopsies, and Magnetic Resonance Imaging (MRI) and Magnetic Resonance Spectroscopy (MRS) will be performed. During these two visits, bioelectrical impedance will be conducted to screen body composition and resting energy expenditure (REE) will be determined. Also, ergospirometry test will be performed to determine the intensity of the individually prescribed training program and the efficacy of the exercise intervention. Exercise habits will be assessed by a questionnaire for the entire 12-week intervention period. Additionally, an objective physical activity monitoring will be performed through the intervention. Subjects will also fill in online questionnaires regarding their food intake for one week prior to each visit. Glucose monitoring will be conducted for 4 weeks during the intervention, 2 weeks at the baseline and 2 weeks before the end of the intervention to screen the effect of the exercise on glucose metabolism.

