# STUDY DESIGN

This study is designed as an intervention study in which subjects will follow the 12-week exercise intervention. Subjects will receive instructions for a high-intensity aerobic interval training (HI) (described below). Dietary intake will remain unchanged. The first part of the study is conducted with 15 subjects. This is followed by an interim analysis and based on the results of this analysis, the intervention will be extended with another 15 subjects based on approval by the IRB. The study design is presented in figure 1.

Complementary study

Baseline

Mid-intervention

Final intervention

Interim analysis

Diagnosed NAFLD

(5.5 % > liver fat)

BMI < 40 kg/m^2^

18–70 years of age

n=15

Ergospirometry test

Anthropometrics

Food records

REE

Oral swab

Stool and urine samples

MRI and MRS

Blood samples

Liver, adipose tissue and muscle biopsies

Ergospirometry test

Anthropometrics

Food records

REE

Oral swab

Stool and urine samples

MRI and MRS

Blood samples

Liver, adipose tissue and muscle biopsies

Body weight

Food records

Oral swab

Stool samples

Blood samples

Exercise intervention – pilot study

Screening

Week 0

+/- 3 week

Identical to pilot study,

recruitment of

additional subjects

+/- 3 months

Continous glucose monitoring

Continous glucose monitoring

Week 12

+/- 3 week

Week 6

+/- 2 week

Figure 1 Overview of the study design with the main procedures that will be performed during the 12-week exercise intervention.

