# METHODS

## Study parameters/endpoints

### Main study parameter/endpoint

Main study parameters and endpoints include:

- NAFL disease progression, evaluated by liver biopsy and MRI/MRS scan. This is based on analysis between baseline and endpoint.
- Hepatic, muscle and adipose tissue histology and gene expression (evaluated by RNA-sequencing) that is affected by exercise intervention. This is based on liver, muscle and adipose tissue biopsy at baseline and endpoint.

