## Randomisation, blinding and treatment allocation

Not applicable.

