# STATISTICAL ANALYSIS

## Primary study parameter(s)

Statistical analyses will be performed by SPSS statistical analysis software. Normality of the data will be assessed by a Kolmogorov–Smirnov test. Data transformation will be done if the data is not normally distributed. The primary analyses of studied primary parameters will be performed between the baseline and endpoint intervention by analysis of one-sample t-test, or chi-square test. If the data is not normally distributed and data transformation is not possible, the Mann-Whitney test will be used. Further associations will be assessed with Pearson rank correlation test / Pearson chi-square test.

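### A liver biopsy from up to 12 months before screening may replace the week-0 biopsy, so for some subjects the paired liver-tissue change is not a 12-week change

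*Protocol*

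**What the plan says.** Section 6.3.13 places the ultrasound-guided liver biopsy at the baseline and endpoint visits, and then adds: "If a liver biopsy is already performed 12 months prior to screening, no need for baseline biopsy". The waiver sets no condition on how the earlier sample was taken or stored, or on what has changed since.

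Three other places carry no such exception:

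- The summary, on burden and risks: "At the baseline (first) and endpoint (final) visit we will collect (ultrasound guided) liver, muscle and subcutaneous adipose tissue biopsies".
- Section 2 (Objectives), which lists the liver biopsy among the items collected at baseline and endpoint.
- Section 6.1.1, which defines one main endpoint as "NAFL disease progression, evaluated by liver biopsy and MRI/MRS scan. This is based on analysis between baseline and endpoint" and says of tissue histology and gene expression: "This is based on liver, muscle and adipose tissue biopsy at baseline and endpoint".

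On design, section 3 says: "This study is designed as an intervention study in which subjects will follow the 12-week exercise intervention". There is no control group. Section 8.1 says: "The primary analyses of studied primary parameters will be performed between the baseline and endpoint intervention by analysis of one-sample t-test, or chi-square test".

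**The concern.** The main liver-tissue outcome is a before-and-after difference in one group. Everything that happens to the liver between the two biopsies is counted as exercise effect, so the difference can be interpreted only if the first biopsy sits at the start of the exercise period. The waiver gives this up for an unknown number of subjects.

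The protocol itself treats the influences that could act in the extra time as important. Sections 5.1 and 6.3.2 ask subjects to keep their diet stable, and 5.1 asks the same for weight. Section 6.4.1 withdraws a subject whose drug prescriptions change during the study. Section 4.3 excludes regular exercise or diet programmes, but only for the 3 months before recruitment. A biopsy 12 months old leaves roughly nine further months that this criterion does not cover.

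Two further consequences follow:

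- **Timing across tissues.** The muscle, fat, stool and MRI/MRS baselines have no waiver. An old liver sample would be related to measurements taken at another time, although the objectives are about those relations.
- **Usable tissue.** Section 6.3.13 requires fasting and frozen storage for study biopsies but does not ask this of the earlier one. Some pairs may have no RNA-seq result at one end.

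**Working it through.** **Sample size in section 4.4.** The 28 cannot be uniquely reproduced, because no SD, rates or correlation are given. One guess, a chi-square test of 100% versus 75% in two independent groups, gives 27 per group (34 with continuity correction). For dropout, 28/0.9 = 31.1, so 32, and 28 × 1.1 = 30.8, so 31; the protocol states 30. The point does not rest on these figures.

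**Interval between paired biopsies.** Inputs: 12 months, about 52 weeks (6.3.13); 12 weeks of intervention (section 3); windows of ±3 weeks at week 0 and week 12 (Figure 1).

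| Case | Interval (weeks) | Share covered by exercise |
| --- | --- | --- |
| Biopsy at week 0 | 12 | 12/12 = 100% |
| Biopsy 1 month before screening | 4.3 + 12 = 16.3 | 12/16.3 = 74% |
| Biopsy 12 months before screening | 52 + 12 = 64 | 12/64 = 19% |
| The same, both windows used in full | 52 + 12 + 3 + 3 = 70 | 12/70 = 17% |

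The longest intervals are 64/12 = 5.3 and 70/12 = 5.8 times the planned one. Except for the windows in the last row, the gap from screening to week 0 is ignored; the protocol does not fix it.

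**Illustration 1: lost RNA pairs.** Assume a paired t-test, two-sided 5%, with 80% power at 28 pairs. The noncentral t distribution then gives a standardised effect d_z = 0.549. Keeping that effect:

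- 20% lost: 28 × 0.8 = 22.4, so 22 pairs, power 69%.
- 40% lost: 28 × 0.6 = 16.8, so 17 pairs, power 57%.

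**Illustration 2: drift before week 0.** For a 25% fall, d_z = 0.549 implies an SD of change of 0.25/0.549 = 0.455. Assume that expression fell by 5–15% between the old biopsy and week 0, and that exercise does nothing. The mean change is then shifted by share × drift:

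- One quarter of subjects waived: 0.25 × 0.05 = 0.0125 to 0.25 × 0.15 = 0.0375.
- One half waived: 0.5 × 0.05 = 0.025 to 0.5 × 0.15 = 0.075.

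Against the 25% target, that is 0.0125/0.25 = 5% up to 0.075/0.25 = 30%. In simulation (40,000 runs) the false-positive rate at n = 28 is 5.0–6.8% with a quarter waived and 5.6–12.8% with half. At n = 15 it is 5.1–5.7% and 5.5–9.2%. A rise before week 0 would instead hide a benefit.

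For gene expression the two harms are alternatives within a subject: a sample without RNA cannot bias the RNA change.

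**The case against.** The strongest reply is about scope. Only liver-biopsy outcomes are touched, and only in subjects who use the waiver; there may be none. MRI/MRS liver fat, which is also part of the main endpoint, keeps its week-0 baseline, as do the muscle and fat biopsies. This stands, and the point is limited accordingly.

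Secondly, the earlier biopsy might be a good sample. A reader might infer that it is a routine clinical specimen, but 6.3.13 says only that a liver biopsy was performed. The summary describes the sponsor's own biopsy-proven cohort and an earlier liver gene expression study, so it could be a research specimen. Loss of RNA is therefore possible, not established.

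Thirdly, the share of waived subjects, the drift and the paired t-test are not in the protocol, and section 4.4 names a chi-square test. This also stands: the power and false-positive figures show what could happen and are not estimates. Likewise, 17–19% is the worst case and not typical; a recent biopsy does much less harm.

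A reader might go further and infer from section 6.2, whose whole text is "Not applicable", that the protocol rules out masked reading of slides and scans. It does not support that. The heading covers randomisation, blinding and allocation together in a single-group study and never mentions reading. The protocol is silent on the matter, and such detail is commonly left to other documents.

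None of this removes the contradiction, or the fact that a later analysis plan cannot supply a week-0 sample that was never taken.

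**Conclusion.** The point holds for the liver-biopsy outcomes, histology and RNA-seq. Section 6.3.13 contradicts the summary, section 2 and section 6.1.1 on whether every subject has a liver biopsy at baseline. For a subject who uses the waiver, the measured change may span up to 64–70 weeks, of which 12 are exercise. With no control arm the remainder cannot be separated from the effect, and its direction is unknown. The interval figures rest on reading the waiver as within 12 months, which is the natural sense although the sentence does not say so.

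The overall effect on the trial cannot be given from the protocol. Under the stated assumptions it runs from negligible, with few waived subjects and little drift, to a false-positive rate of about 13% with half of 28 subjects waived, or a power of about 57% with 40% of RNA pairs lost. The first stage deserves attention: section 4.4 uses liver expression in only 15 subjects to revisit the sample size, so a few mixed intervals could distort that decision.

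**What to change.** 1. Reconcile section 6.3.13 with the summary, section 2 and section 6.1.1, so that all four say the same about which subjects have a liver biopsy at baseline. Which biopsy rule to keep is for the sponsor to settle.
2. State in section 8.1 that the primary paired analysis of liver histology and liver RNA-seq uses only subjects whose two liver biopsies were both taken under the protocol. Apply this also to the interim check of liver expression, including PNPLA3, in section 4.4.
3. Show subjects with a waived baseline biopsy in a sensitivity analysis, with the date of the earlier biopsy.
4. Report the number of evaluable liver pairs, separately for histology and RNA-seq, at the interim and at the end.

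The cost is wording, and fewer pairs in the primary liver-tissue analysis if the waiver is used. Waived subjects still contribute to the MRI/MRS, muscle, fat and microbiota analyses. No replacement enrolment and no added biopsy is asked for. If the sponsor wanted to restore the lost pairs by enrolling more subjects, that would mean further invasive procedures and would be a separate decision.

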### Muscle biopsies

Muscle biopsies are carried out under sterile conditions and local anaesthesia (lidocaine 20 mg/ml (2 %), approximately 5 ml subcutaneously) at baseline and final intervention visits as previously described (2014_084). An incision will be made in the muscle and a biopsy will be taken. The biopsy specimen will be washed in a buffer (NaCl 0.9% / Hepes 28.3 gr/L) to remove blood. It will then be inspected for fat or fascia content and dried on gauze swabs, and subsequently stored in both formalin/paraffin and frozen in liquid nitrogen after extraction, and stored at -80°C until analysis. These biopsies will be used to estimate gene expression using RNA-sequencing.

### Subcutanous adipose tissue biopsies

At baseline and endpoint visits subcutaneous fat aspirates will be performed as previously described (2013_207). Biopsies will be carried out under sterile conditions and local anaesthesia (lidocaine 20 mg/ml (2 %), approximately 5 ml subcutaneously). Fat tissue will be obtained by hollow needle suction in the peri-umbilical area (thus no incision will be made). One half of a sample will be stored at -80°C until analysis. Haemostasis will be attained by providing local skin pressure, and suture strips will be used to close the wound and a pressure bandage will be given to minimize changes of local haematoma.

### Storage for further analysis

Samples will be stored for 15 years in biobank of the department of vascular medicine of the AMC (“Biobank vasculaire geneeskunde AMC”) in line with all applicable regulations and laws for future additional analysis. A separate protocol for the storage in the biobank will be simultaneous submitted to the “biobank toetsingscommissie”.

## Withdrawal of individual subjects

Subjects can leave the study at any time for any reason if they wish to do so without any consequences. In this case, financial compensation will be calculated based on extent of participation. The investigator can decide to withdraw a subject from the study for urgent medical reasons.

### Specific criteria for withdrawal (if applicable)

Participants with any new condition during the study that require hospital admission, change in drug prescriptions or likely to affect the outcome of this study will be withdrawn. Participants will also be withdrawn if instructions as written in the protocol are not followed.

## Replacement of individual subjects after withdrawal

Withdrawn subjects will be replaced in order to attain the desired sample size.

## Follow-up of subjects withdrawn from treatment

Subjects withdrawn for medical reasons will be followed until the interfering condition has resolved or reached a stable state.

## Premature termination of the study

Not applicable since no medicinal product is involved and since this entails a pilot study of 15 participants.

# SAFETY REPORTING

## Temporary halt for reasons of subject safety

In accordance to section 10, subsection 4, of the WMO, the sponsor will suspend the study if there is sufficient ground that continuation of the study will jeopardise subject health or safety. The sponsor will notify the accredited METC without undue delay of a temporary halt including the reason for such an action. The study will be suspended pending a further positive decision by the accredited METC. The investigator will take care that all subjects are kept informed.

## AEs and SAEs

### Adverse events (AEs)

Adverse events are defined as any undesirable experience occurring to a subject during the study, whether or not considered related to the experimental intervention. All adverse events reported spontaneously by the subject or observed by the investigator or his staff will be recorded.

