## Follow-up of adverse events

All AEs will be followed until they have abated, or until a stable situation has been reached. Depending on the event, follow up may require additional tests or medical procedures as indicated, and/or referral to the general physician or a medical specialist. SAEs need to be reported till end of study within the Netherlands, as defined in the protocol.

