## Benefits and risks assessment, group relatedness

Participant may benefit in the short term from the exercise since it may improve their physical fitness and motivation to actively perform exercise. Additionally, patients are helping to further unravel the relation between exercise induced changes in gut microbiota in relation to metabolic control in liver, muscle and adipose tissue which may lead to novel diagnostic and therapeutic leads

The placing of the intravenous cannula in our study can be an unpleasant experience for the subjects and may result in (self limiting) bruising.

An experienced interventional radiologist will perform ultrasound-guided liver biopsy. Ultrasound-guided percutaneous liver biopsy is a safe method with very low the risk of complications (< 0.1 %) comprising mostly bleeding from the biopsy site. Moreover, local hemostasis after the procedure can be observed. Liver biopsy will be performed under local anaesthesia.

Adipose tissue biopsy will be taken from the fat of the abdomen. The abdominal skin will be anesthetized at the site of the biopsy so it will be painless for the participants. However, it is unpleasant but not harmful since anaesthetic is a small prick and may feel uncomfortable. In few hours after the biopsy, the area of biopsy may feel a bit sore and a bruise may develop.

Muscle biopsy will be taken from the muscle of leg under aesthetic conditions. Following a muscle biopsy the leg may stay sensitive for a few days. It is a minor intervention, usually without any events but like any procedure there is a minor risk of bleeding or infection.

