## Temporary halt and (prematurely) end of study report

The investigator/sponsor will notify the accredited METC of the end of the study within a period of 8 weeks. The end of the study is defined as the last patient’s last visit.

The sponsor will notify the METC immediately of a temporary halt of the study, including the reason of such an action.

In case the study is ended prematurely, the sponsor will notify the accredited METC within 15 days, including the reasons for the premature termination.

Within one year after the end of the study, the investigator/sponsor will submit a final study report with the results of the study, including any publications/abstracts of the study, to the accredited METC.

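### No safety contact is planned after the final visit, where the second liver, muscle and fat biopsies are taken, so delayed complications of about half of all biopsies are captured only if volunteered

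*Protocol*

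**What the plan says.** Section 7.2.1 of the protocol sets the time frame and the method for adverse events. The time frame is the study: "Adverse events are defined as any undesirable experience occurring to a subject during the study". The method is passive: "All adverse events reported spontaneously by the subject or observed by the investigator or his staff will be recorded". No direct question to the subject is described.

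Section 7.3 limits serious events: "SAEs need to be reported till end of study within the Netherlands, as defined in the protocol". Section 10.5 supplies the date: "The end of the study is defined as the last patient’s last visit".

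The Summary, in its paragraph on burden and risks, fixes when tissue is taken: "At the baseline (first) and endpoint (final) visit we will collect (ultrasound guided) liver, muscle and subcutaneous adipose tissue biopsies". Section 6.3.13 allows the first liver biopsy to be skipped: "If a liver biopsy is already performed 12 months prior to screening, no need for baseline biopsy". It also gives the only stated period of observation after a biopsy: "The subject is then instructed to lie on his/her right side for 1-2 hours after the test", with pulse, blood pressure and temperature checked. Sections 6.3.14 and 6.3.15 state no observation period for the muscle and fat biopsies.

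Section 9.3 describes what may follow. For muscle: "Following a muscle biopsy the leg may stay sensitive for a few days", with a minor risk of bleeding or infection. For fat, it mentions soreness and possible bruising in the hours afterwards.

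**The concern.** The period in which the protocol expects procedural effects (hours to a few days) is longer than the period in which it plans to look (1-2 hours, after the liver biopsy only). After the baseline biopsies this gap is largely closed in practice, because section 5.1 brings subjects back twice a week for closely supervised training, where staff can see or hear of a problem. After the final biopsies nothing comparable is planned. The two biopsy rounds are therefore observed with different completeness by design.

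What is at stake is the complication record. Following the plan exactly as written would tend to under-count delayed complications of the second round, and any complication rate per biopsy would be biased low. The biopsies are the main invasive burden, and a possible second group of 15 subjects would go through the same procedures. This is not detail left to a statistical analysis plan: how events are captured, the safety window and the end of study are all fixed in protocol sections 7.2.1, 7.3 and 10.5.

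**Working it through.** The protocol gives no figure for the share of biopsies without later capture, so there is nothing to reproduce. The share can be counted.

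**Inputs**
- 15 subjects first, possibly 15 more (section 3).
- 3 tissues at 2 visits (Summary).
- About 10% dropout (section 4.4), with replacement of withdrawn subjects (section 6.5).
- Possible waiver of the baseline liver biopsy (section 6.3.13).

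**Share of biopsies at the final visit = final biopsies / all biopsies**

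| Scenario | Baseline | Final | Share at final visit |
| --- | --- | --- | --- |
| 15 complete, none waived | 15 × 3 = 45 | 15 × 3 = 45 | 45/90 = 50% |
| 10% dropout, replaced (15/0.9 = 16.7, so 17 enrolled) | 17 × 3 = 51 | 45 | 45/96 = 46.9% |
| All baseline liver biopsies waived, all complete | 15 × 2 = 30 | 45 | 45/75 = 60% |

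The dropout row assumes that withdrawals happen after the baseline biopsies. With 30 subjects the counts double and the shares are the same (90/180 = 50%; 34 enrolled gives 90/192 = 46.9%).

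**Biopsies with no open reporting window at all**

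The end of study is one date for the whole trial. Only the last subject's final biopsies coincide with it: 3/90 = 3.3% with 15 subjects, or 3/180 = 1.7% with 30, assuming that no two subjects share the last date.

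**Upper bound on the effect on the complication record**

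The Summary expects about 1 patient with a complication in the entire study. Assume a Poisson count, spread evenly over the two rounds, and suppose every final-visit event is lost:
- P(none recorded), full capture = exp(−1) = 0.37.
- P(none recorded), final round lost = exp(−0.5) = 0.61.

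This is an upper bound, because events in the first 1-2 hours would be seen and some later ones would be volunteered. It also depends on which of the protocol's own figures is used. The same part of the Summary puts the liver-biopsy risk below 0.1%. Over 30 liver biopsies that is at most 30 × 0.001 = 0.03 events, and the same calculation moves P(none recorded) only from exp(−0.03) = 0.970 to exp(−0.015) = 0.985. The two statements do not agree, so the size of the loss lies somewhere between negligible and this bound.

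**The case against.** The strongest case on the other side is that the formal window is open for nearly everyone. A reader might infer that complications after at least half of all biopsies fall outside the safety window. The documents do not support that. The end of study is the last patient's last visit, not each subject's own, so for every earlier subject an event after the final biopsies still occurs during the study and must be recorded if it becomes known. The words at least half are not guaranteed either, because replaced subjects may contribute baseline biopsies only.

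A reader might also infer that a delayed complication would not reach the ethics committee. That goes too far. Section 7.2.2 requires the investigator to report every SAE after learning of it, and the sponsor to pass it on within 7 or 15 days. Some subjects come from the centre's own clinics, and those found to have NASH at baseline are referred there, so contact may continue.

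Two further inferences fail. The complication rate below 0.1% in section 6.3.13 rests on hospital experience and a cited publication, so this trial's count does not underlie it. The extension to 30 subjects is tied to gene-expression findings, the power calculation and IRB approval (sections 3 and 4.4), and nowhere to complication counts.

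It is also fair to say that section 7.2.1 does not forbid asking, that known events are followed until resolved or stable (section 7.3), that aftercare instructions may stand in the earlier protocols cited for the biopsies or in the separate patient information letter, and that the Summary mentions six site visits without fixing the order of all endpoint procedures. Some subjects may therefore have a contact after their final biopsies.

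All of this narrows the point without removing it. An open window with no planned enquiry depends on the subject volunteering the event, and nothing in this protocol guarantees a contact after the second round.

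**Conclusion.** The point holds as a gap in planned capture, not as a closed window. About half of all biopsies (50% if all subjects complete, 46.9% with 10% dropout and replacement, up to 60% if all baseline liver biopsies are waived) have no planned means of picking up complications that appear after the visit, although section 9.3 expects effects over hours to a few days. For the last subject only, 3 of 90 biopsies, the SAE reporting period ends on the biopsy day itself.

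The conclusion rests on two readings: that the final biopsies are taken at the last visit, as the Summary says, and that no separate document provides a later contact. The consequence is a complication record biased low for the second round. The shift in the chance of recording no complication, from 37% to 61%, is an upper bound under the Summary's expectation of about 1 complication, and it almost vanishes under the rate below 0.1% given in the same place. The efficacy analyses are not affected. The change is worth making because it is small and closes the gap fully.

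**What to change.** In sections 7.2.1 and 7.3, add one solicited safety contact per subject after each biopsy visit, for example a telephone call that asks directly about complications of the biopsies. The investigators should set the interval so that it covers at least the few days that section 9.3 already expects. In section 10.5, define the end of study as the last subject's post-biopsy safety contact, so that the SAE reporting period in section 7.3 stays open until then for everyone. Report complications per biopsy and by biopsy round.

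The cost is about 15 × 2 = 30 short calls for 15 subjects (60 for 30), a few sentences in an amendment, and a study end that moves by a few days. The recorded complication rate may look less favourable, because more events will be found. No further visit or invasive procedure is needed.
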